#### 2.2.3. Collecting Discarded Packs from Trash Recycle Markets

A common practice in Bangladesh is to recycle waste papers, including cigarette packs, which are then used as raw material in paper mills. Large municipal cities in urban areas locally known as “City Corporations” have a trash collection system. They collect trash from confined areas and from street corners where the trash bins are placed. A trash recycle market exists in some places to collect used papers and cigarette packs, but this is limited in rural areas. If a trash recycle market exists in the sample areas, and we are able to obtain the empty packs, we will include them in the study. 

#### 2.2.4. Interview of Point of Sale Retailers

During bag collection, basic information such as name and type of the store, price and estimated quantity of the cheapest brand sold in the shop, name and price of most popular brand, and the estimated quantity sold will be collected. In addition, they will be asked about the profit share of tobacco products in their total daily profit, sources of supply, incentives from the suppliers’ end, market supervision, and knowledge, understanding, and perception regarding illicit tobacco products. A structured questionnaire that has been used in studies in the UK, Bangladesh, Nepal, and Pakistan previously will be adapted to collect these data from the retailers [19]. Following the Tobacco Advertisement and Promotion Survey (TAPS) [20], a standard pack analysis tool has been developed. 

#### 2.2.5. Field Design and Implementation

Ten data collectors will be recruited and attend a one-day training session on: (a) getting packs from retailers; (b) getting packs from the streets; and (c) collecting packs from trash recycle market. The in-house training will focus on the ways of finding the public gathering places, selecting the retailers, instructing the retailers about pack preservation for the day maintaining certain qualities, and collecting the packs. They will also receive training on obtaining informed and written consent, how to generate the “Unique ID” for the “Collection Bags”, how the packs should be preserved, and how to collect discarded packs from the streets. The data collection would be carried out during the period February 2020 to September 2020 and the analyses be performed by March 2021.

The Research Fellow and one field supervisor will visit the study sites during data collection period to check the survey is done properly. They will also visit a subset of the chosen retailers. Data will be monitored for quality and completeness by the core research team. Due to the sensitive nature of the research study, we will make our best efforts to provide security measures to our data collectors. We will group the data collectors together, whenever possible. We will prescribe specific hours for data collection, outside of which data collectors will not be allowed to collect data. Every data collector will have a cell phone with pre-paid credit and a dedicated team member will be on-call during the prescribed data collection time, to provide assistance regarding the questions or any issue in the field. 

All the collection bags will be brought back to the research office where we will have data entry operators to inspect the packs and register their characteristics into the database for further analysis. The training for data entry operators will take place with the direct support from National Board of Revenue (NBR) officials in Bangladesh. The relevant officials will be invited to share the techniques and expertise they employ when they examine the authenticity of tax stamps on cigarettes. 

#### 2.2.6. Ethical Considerations

The primary principles of good ethical practice such as autonomy, justice, beneficence, and non-maleficence will be maintained during the study. We are conscious that retailers could have concerns that the research may negatively impact their business, and interviewers could feel uncomfortable during the interaction with retailers. We will adopt multiple measures to mitigate these concerns. First, all potential retailers will be provided with information regarding the project and written consent will be taken prior to data collection. Those who do not agree to participate after reviewing the study information will not be enrolled in the study. The reasons for declining to participate in the study will be recorded. Second, retailers will be reassured that all information collected during the course of the study will be kept strictly confidential. Third, researchers will be trained on techniques for handling conflict, threats, abuse, or compromising situations. We will specifically train researchers to ask questions in a non-judgmental manner and not to put any pressure on the respondents, if they show signs of reluctance in answering one or more questions. Our data collection team will be respectful to the retailers and will avoid interference with the normal flow of business. Interviewers will only continue the interview when the retailer is not dealing or in the vicinity of customers. Every interviewer will have the right to decline collecting packs from a retailer in a location that makes him or her feel unsafe. 

The primary principles of good ethical practice such as autonomy, justice, beneficence, and non-maleficence will be maintained during the study. We are conscious that retailers could have concerns that the research may negatively impact their business, and interviewers could feel uncomfortable during the interaction with retailers. We will adopt multiple measures to mitigate these concerns. First, all potential retailers will be provided with information regarding the project and written consent will be taken prior to data collection. Those who do not agree to participate after reviewing the study information will not be enrolled in the study. The reasons for declining to participate in the study will be recorded. Second, retailers will be reassured that all information collected during the course of the study will be kept strictly confidential. Third, researchers will be trained on techniques for handling conflict, threats, abuse, or compromising situations. We will specifically train researchers to ask questions in a non-judgmental manner and not to put any pressure on the respondents, if they show signs of reluctance in answering one or more questions. Our data collection team will be respectful to the retailers and will avoid interference with the normal flow of business. Interviewers will only continue the interview when the retailer is not dealing or in the vicinity of customers. Every interviewer will have the right to decline collecting packs from a retailer in a location that makes him or her feel unsafe. 

The study has been granted ethics approval by the National Research Ethics Committee of the Bangladesh Medical Research Council (Ref: BMRC/NREC/2016–2019/344; Registration Number: 241 05 08 2019) and the Health Sciences Research Governance Committee at the University of York (HSRGC/2019/346/A, approval date 5 July 2019). 

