#### 2.2.1. Collecting Packs from Tobacco Retailers

The data collection team will determine a central point (such as a bus station, a government building, or a market place) in each PSU. All types of shops, such as tea stalls, kiosks, supermarkets, department stores, and cigarette shops that sell cigarettes or birri, or both, would be eligible to take part in the study. Enumerators will walk half a kilometer in both directions on the main street around the public gathering place and approach all the retailers meeting the eligibility criteria. All eligible retailers will be provided with both verbal and written information about the study. If they agree to take part, they will be required to sign the consent form. Following consent, the field worker will proceed to pack collection. The retailers would be supplied with a “collection bag” on the previous day and asked to keep all the empty packs resulted from loose sale on the following day since the shop opened in that bag. All “collection bags” will be retrieved by the field workers at the end of the business day. We will provide a small monetary reward of BDT 3 (GBP 0.03) per empty pack deposited in the collection bag. In case the empty pack of the cheapest and popular brands were not available in the bag from a particular retailer, the team would take a picture and code all the relevant attributes of such pack observed in the shop itself [3]. 

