Another important potential limitation of the proposed methodology would be its ability of correct estimation for the size of illicit market. Since the unit of observation from where packs would be collected is retail cigarette shops, selection bias might remain present in the estimation. The estimate would be overestimated if pack collection takes place in an area where illegal tobacco products are known to be traded. In contrast, the estimates would be underestimated if retailers purposefully preserve the licit cigarette packs in the collection bag. Moreover, conditioning that illicit cigarettes are sold in full packs in general rather than single sticks, collecting empty packs from retailers might underestimate the magnitude. Considering all these potential threats, we expect the study would be free from selection bias as the retailer selection would be completely random covering the urban–rural and border–non-border perspective around the country. The validity and representativeness of the estimate measured using the packs collected from retailers would be ensured by comparing that with the estimate retrieved from littered packs from the streets and packs collected from the trash recycle market in the same neighborhood. Estimates from the two later sources to a greater extent would address the limitations if retailer deposit only licit packs or illegal cigarette happens to be sold in full pack. The comparison of results and further analysis of illicit packs from these three sources would help us to examine the existence of any systematic difference among them. Absence of systematic difference would ensure the possible unbiasedness of the estimates [12].

Finally, in the absence of any prevalence data at the division or district level, it would not be possible to propose a sample size weighted on the local smoking prevalence or smoking intensity. Bangladesh has completed two rounds of Global Adult Tobacco Survey (GATS). However, the first round does not have district level or divisional level information on smoking prevalence while the data from second round have not been released yet. 

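### The Discussion expects no selection bias because retailer selection is random, but only the areas are drawn at random: consent and interviewer discretion decide which shops give packs

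*Protocol article*

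**What the plan says.** Section 2.1 draws districts and then post codes at random. Section 2.2.1 makes no random draw of shops. The team fixes a central point in each post code, walks half a kilometre each way along the main street, and is to "approach all the retailers meeting the eligibility criteria". Each retailer is informed about the study verbally and in writing, and pack collection follows only after consent: "If they agree to take part, they will be required to sign the consent form".

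Section 2.2.6 adds two ways in which an approached or eligible shop drops out:

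- Refusal: "Those who do not agree to participate after reviewing the study information will not be enrolled in the study". On what is kept about refusers it says "The reasons for declining to participate in the study will be recorded".
- Interviewer discretion: "Every interviewer will have the right to decline collecting packs from a retailer in a location that makes him or her feel unsafe".

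The same section recognises a motive for reluctance, namely that "retailers could have concerns that the research may negatively impact their business".

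Section 3 (Analysis Plan) reports frequencies and proportions of non-compliant packs, with each source analysed separately. The Discussion first allows that selection bias might be present. It names three threats: areas known for illegal trade, retailers who deposit only licit packs, and illicit cigarettes sold as full packs. It does not name refusal or skipped shops, and then concludes: "we expect the study would be free from selection bias as the retailer selection would be completely random".

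**The concern.** The reason given for expecting no selection bias is a property the design does not have. Random choice of post codes controls which areas are studied. It does not control which shops in those areas agree to hand over packs for inspection. A shop that sells illicit packs has more to lose from inspection than a compliant one, so refusal may be related to the quantity being estimated.

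The retailer sample answers question (a), the illicit proportion of cigarettes sold at retail. It also supplies DF_R, the retailer duty-free proportion that caps the corresponding street figure in Section 3, with a similar process for trash packs. The study is meant to answer industry claims. A retailer share that may be too low, presented as free from selection bias, is open to attack.

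**Working it through.** The protocol gives no refusal rate, number of retailers or precision target, so there is no figure of its own to reproduce on this point. The check is how far the retailer share moves when refusers differ from participants.

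**Inputs**

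- T: true illicit share of retail pack volume. For illustration, the Introduction gives 2% (industry-based claim for Bangladesh) and 16.8% (LMICs).
- r: fraction of pack volume sold by non-participating shops. Assumed, 10% to 50%.
- k: their illicit share divided by the participants' share. Assumed, 0.5 to 5.

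**Formula**

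With p the share seen among participants, T = (1 − r)p + r·k·p. Hence p = T / [(1 − r) + r·k], and the relative bias is 1 / [(1 − r) + r·k] − 1, whatever T is.

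| k | r = 10% | r = 20% | r = 30% | r = 50% |
|---|---|---|---|---|
| 0.5 | +5.3% | +11.1% | +17.6% | +33.3% |
| 1 | 0 | 0 | 0 | 0 |
| 2 | −9.1% | −16.7% | −23.1% | −33.3% |
| 3 | −16.7% | −28.6% | −37.5% | −50.0% |
| 5 | −28.6% | −44.4% | −54.5% | −66.7% |

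Example with r = 30% and k = 3: the divisor is 0.7 + 0.3 × 3 = 1.6. A true 2% is seen as 2 / 1.6 = 1.25%, and a true 16.8% as 16.8 / 1.6 = 10.5%.

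**Carry-over to street and trash**

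Section 3 sets the illegal duty-free proportion in litter to DF_R if DF_L > DF_R, and to DF_L otherwise. This is the smaller of the two. Take assumed values of a true retailer duty-free proportion of 1.0% and DF_L = 1.5%. With r = 30% and k = 3, DF_R is seen as 1.0 / 1.6 = 0.625%, so the street figure becomes 0.625% instead of 1.0%. If DF_L does not exceed the observed DF_R, refusal has no effect. Table 3 marks wider classes of street and trash packs for adjustment, but the only formula given is for duty-free packs.

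**What the planned comparison can show**

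Where the cap applies, the adjusted street duty-free figure equals DF_R, so the two agree by construction. The adjusted street figure can never exceed the retailer one. On this component the comparison cannot show that the retailer figure is too low. On the other criteria (price, brand element, warnings, declaration, tax stamp) that formula imposes no cap, and a gap can appear.

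**The case against.** The strongest reply is that the design has a check. Street packs are collected along the streets where the retailers trade and need no retailer's consent, so packs sold by refusing shops can enter that sample. The Discussion compares the three sources for systematic differences. This stands as far as it goes: the comparison could expose a retailer share that is too low. It does not correct that share, the duty-free cap removes part of the signal, and Section 2.2.3 says trash markets are limited in rural areas, which are 40 of the 80 post codes (8 districts × 5).

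Several stronger readings are tempting, and the documents do not support them:

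- *All three estimates are pulled down together.* DF_R enters only the duty-free component, one of seven criteria, and only where DF_L > DF_R.
- *Nothing but the reason for refusal is kept.* The text says reasons will be recorded; it does not say nothing else will be. Logs, participation rates and weights may sit in a fuller document that is not shown.
- *The retailer share is shown to be too low.* Many criteria are printed pack features, such as a descriptor or the layout of a warning, and a shopkeeper may not know that they breach the rules. Refusal need not follow the study definition. Nor does the article say that retailers are told the study concerns illegal sales.
- *Not enrolling refusers is itself an error.* It is an ethical requirement, as is the interviewers' right to stay away. Neither should change.

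The point therefore rests on what the Discussion asserts, not on missing detail.

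**Conclusion.** The statement expecting freedom from selection bias is contradicted by Sections 2.2.1 and 2.2.6 and should not stand. Bias from refusal or skipped shops is absent only if those shops sell the same illicit share as participants, and random choice of areas does nothing to secure that.

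A downward bias in the retailer share is plausible but unproven. Over the assumed range (non-participants with 10% to 50% of volume and 2 to 5 times the illicit share) it is −9% to −67% in relative terms. With half the share it is +5% to +33%. Both r and k are assumptions, so the table shows sensitivity and does not estimate the bias. Any effect on street and trash is confined to the duty-free component where the cap applies.

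**What to change.** 1. Delete the statement that the study is expected to be free from selection bias, and name refusal and skipped shops as threats beside the three already listed.
2. Log post code and visible shop type for every approached, refusing or skipped shop, and report participation rates. The log gives the fraction of shops, not of volume, so r should be varied around it.
3. Report the retailer share with non-participants at, for example, 0.5, 1, 3 and 5 times the participants' illicit share. The range must be two-sided.
4. Show the street and trash duty-free figures with and without the DF_R cap.
5. Treat any association across post codes between refusal rate and street illicit share as exploratory, since border location or enforcement could raise both. Do not rely on weights by post code and shop type to remove the bias: they assume that refusers resemble participants of the same type, which is the point in doubt.

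The cost is one log line per shop, a sensitivity table and a changed sentence. The retailer figure will be wider and less favourable.

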## 3. Analysis Plan

We will classify a cigarette pack as illicit if it has at least one of the following attributes: No mention of “retail price”: It is mandatory to print the retail price of the goods “on the body of the goods or on every package, sachets or cells distinctly, conspicuously and indelibly”. This applies to cigarettes, and packs not containing the retail price can be considered illegal [21].Mention of brand element: Packets should not contain any brand elements, for instance Light, Mild, Low Tar, Extra, and Ultra. Packs mentioning brand element will be considered illegal [22].No graphic health warnings: Health warnings shall be printed on both sides of the packet covering at least 50% of the total area of each main display area. In addition, the warnings should be in colored pictures. Rules notified further suggests that the ratio and written warnings should be 6:1 and the written warnings has to be printed in black background with white font color. Packs not fully complying the above rules will be considered illegal [21,22].No textual health warnings: The following warnings should be printed on the packet in Bengali, otherwise it can be considered as illegal [21,22].
(a)Smoking causes throat and lung cancer;(b)Smoking causes respiratory problems;(c)Smoking causes stroke;(d)Smoking causes heart disease;(e)Second-hand smoke causes harms to the fetus;(f)Smoking causes harms to the fetus; or(g)Second-hand smoking causes death.No declaration: Selling of tobacco products without having the statement “Sales allowed only in Bangladesh” printed on the packets would be illegal [22].A duty-free sign: Cigarette packs collected from retailers with a “duty-free” sign will be classified as illegal as these are to be sold in Duty Free shops only and should not be available in the market.Absence of correct and authentic tax stamp/banderole: The government has made it obligatory to use tax stamp or banderole on cigarette packets. Any sale of cigarette without this tax stamp or banderole is legally prohibited. The banderole/stamp of cigarette pack of different size and design had been defined [21]. We will check if the packs have used banderole/stamp correctly as per the SRO and VAT Booklet, and if the banderole/stamp is genuine.

In general, all pack characteristics considered for detecting legitimacy in the retailer sample might also be accepted for those in littered or trash samples. Nevertheless, one of the limitations of the above general approach is that it might fail to distinguish between tax evasion and avoidance. More specifically, there may be some legally purchased duty-free packs as well as those bought from neighboring countries, in a sample from street, while also having illegally purchased and illegally sold packs in the retail shops belonging to that street. This possibility might result in under- or overestimation of the illicit cigarette trade. Hence, it rationalizes the application of an adjustment factor while measuring the magnitude of illicit cigarette in the sample collected particularly from street and trash recycle market. Table 3 exemplifies a thematic presentation of legitimacy criterion of a cigarette pack and adjustment requirement in the estimation. 

Assuming that the littered packs in the streets would by and large reflect the average characteristics of those sold by different retailers on the same street, the following adjustment method would be applied:

Suppose DF_L_ is the proportion of duty-free packs (both legal and illegal) in the littered sample and DF_R_ is the proportion of duty-free packs (all illegal) in retailer sample. Then, the estimated proportion of illegal duty-free packs from littered sample would be
=DF_R_ if DF_L_ > DF_R_; and
=DF_L_ if DF_L_ ≤ DF_R_.   

Similar adjustment process would be followed while estimating extent of illicit cigarette using packs from trash recycle sample. It should be noted here that self-made cigarette using tax-paid tobacco powder or crushed tobacco may not be the scope of current work. However, a pack for a local category of cheap cigarette known as “birri” would be collected and examined for its compliance as per the study definition. Statistical Analysis (STATA) software version 15 would be used. The main statistical analysis will report the frequencies and proportions of cigarette packs that do not comply with the tobacco control laws and falls within the study definition of illicit. 

The packs collected from different sources would be kept in separate bags and analyzed separately. In addition, the features of the respective packs would be recorded in three different databases to find separate estimates of illicit cigarettes. The estimates from first two inter-related methods will be triangulated and hence complementing each other. We will then compare and validate these findings with the third method. Given the availability of the trash market in the study sites, and adequate volume of packs collected from the trash market, the findings will be compared with the first two methods. We will assess the extent to which the result of trash market measure corresponds to first two measures to estimate of illicit trade for its validity. Findings from pack analysis would be further triangulated with the retailer interview findings for better understanding of the pattern of illicit practices in the cigarette market. 

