**Stage - Three (Sub - District)**									
5 UPCs form Each District Covering City Corporation/Metropolitan Area/Municipality Area (Paurasava)	UPC - 1	UPC - 1	UPC - 1	UPC - 1	UPC - 1	UPC - 1	UPC - 1	UPC - 1	**Urban Post Codes (UPC):** In each district UPC would be those areas (Sub - Districts) covering Metropolitan Cities or City Corporation Areas or Municipality Area (Paurasava) **Selection Method:** Simple Random Sampling
	UPC - 2	UPC - 2	UPC - 2	UPC - 2	UPC - 2	UPC - 2	UPC - 2	UPC - 2	
	UPC - 3	UPC - 3	UPC - 3	UPC - 3	UPC - 3	UPC - 3	UPC - 3	UPC - 3	
	UPC - 4	UPC - 4	UPC - 4	UPC - 4	UPC - 4	UPC - 4	UPC - 4	UPC - 4	
	UPC - 5	UPC - 5	UPC - 5	UPC - 5	UPC - 5	UPC - 5	UPC - 5	UPC - 5	
5 RPCs/BPCs form Each District Situated in different Sub Districts (Outside City Corporation/ Metropolitan Area/Municipality Area)	RPC - 1	RPC - 1	BPC - 1	BPC - 1	BPC - 1	BPC - 1	BPC - 1	BPC - 1	**Rural Post Codes/Border Area Post Codes (RPC/BPC):** **No Land Border Area:** RPC would be those areas (Sub - Districts) covering outside Metropolitan Cities or City Corporation Areas or Municipality areas (Paurasava). **Have Land Border Area:** BPC would be those areas (Sub - Districts) covering outside Metropolitan City or City Corporation Areas Municipality areas (Paurasava) as well as sharing land border. **Selection Method:** Simple Random Sampling
	RPC - 2	RPC - 2	BPC - 2	BPC - 2	BPC - 2	BPC - 2	BPC - 2	BPC - 2	
	RPC - 3	RPC - 3	BPC - 3	BPC - 3	BPC - 3	BPC - 3	BPC - 3	BPC - 3	
	RPC - 4	RPC - 4	BPC - 4	BPC - 4	BPC - 4	BPC - 4	BPC - 4	BPC - 4	
	RPC - 5	RPC - 5	BPC - 5	BPC - 5	BPC - 5	BPC - 5	BPC - 5	BPC - 5	

**Table 3 ijerph-17-04791-t003:** Legitimacy Criterion of Cigarette Pack and Bias Correction.

Pack Source	Tax Status	Packaging Compliance	Legitimacy of Cigarette Pack	Bias Correction in Estimate
**Retailers**	Paid	Compliant	Legal	No Adjustment Required
		Not Complaint	Illegal	
	Not Paid	Compliant	Illegal	
		Not Complaint	Illegal	
**Streets/Trash Recycle Market**	Paid	Compliant	Legal	No Adjustment Required
		Not Complaint	Might be Legal or Illegal	Adjustment Applied
	Not Paid	Compliant	Might be Legal or Illegal	
		Not Complaint	Might be Legal or Illegal

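### For duty-free packs, the street and trash adjustment is capped at the retailer proportion, so on that component these sources cannot reveal retailer under-reporting

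*Protocol article*

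**What the plan says.** Protocol article, section 3 (Analysis Plan), explains that street litter may contain "legally purchased duty-free packs as well as those bought from neighboring countries", so that not every such pack is illicit trade. It therefore adjusts the street estimate. The stated premise is that "littered packs in the streets would by and large reflect the average characteristics of those sold by different retailers" on the same street. The inputs are defined next: "Suppose DF_L_ is the proportion of duty-free packs (both legal and illegal) in the littered sample", while DF_R is the duty-free proportion in the retailer sample, all of it counted as illegal. The rule follows: "Then, the estimated proportion of illegal duty-free packs from littered sample would be" equal to "DF_R_ if DF_L_ > DF_R_; and" equal to "DF_L_ if DF_L_ ≤ DF_R". A similar process is to be used for the trash recycle sample.

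Table 3 marks no adjustment for retailer packs. For street and trash packs that are non-compliant or not tax-paid, it gives the status "Might be Legal or Illegal" and indicates adjustment. The only formula printed is the duty-free one.

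Section 4 (Discussion) accepts that the retailer sample may run low, because retailers may put only licit packs in the bag or because illicit cigarettes may be sold as full packs. Its answer is the other two sources: "Estimates from the two later sources to a greater extent would address the limitations if retailer deposit only licit packs", and likewise if illegal cigarettes are sold by the full pack. It then reads a lack of systematic difference between the three sources as support for unbiased estimates. Section 3 also uses the correspondence between sources to judge the validity of the trash method, which is research question (c).

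**The concern.** The two sections ask opposite things of the same figure. If retailers hold back duty-free packs or sell them whole, the expected sign is a littered proportion above the retailer proportion. That is the branch in which the rule discards the littered value and puts the retailer value in its place. The premise of the rule, that litter mirrors retail sales, is also what the comparison of sources is supposed to test. The collection plan weakens that premise further, because section 2.2.2 also takes litter from other locally important streets.

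At stake is how agreement will be read. If the adjusted figures are compared, the duty-free part can match simply because the retailer figure was copied into it, and the match could then be cited as evidence that the retailer estimate is unbiased and the trash method valid.

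**Working it through.** **Inputs from the article.** The two branches of the rule, the definitions of DF_L and DF_R, and the two threats named in section 4. The article gives no duty-free share and no pack count per source, so there is no figure of its own to reproduce. The shares below are assumptions chosen to show the behaviour of the rule.

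**Step 1: what the rule is.** If DF_L > DF_R the result is DF_R; if DF_L ≤ DF_R it is DF_L. In both branches the smaller value is returned, so adjusted = min(DF_L, DF_R) ≤ DF_R. Evaluating the rule on a 201 × 201 grid over 0 to 1 confirms this at every point.

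**Step 2: what happens under the threats in section 4.** Let t be the true illegal duty-free share, g the additional legal duty-free share in litter, and w the fraction of illegal duty-free packs that do not reach the retailer's bag. Then

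DF_R = t(1 − w) / (1 − tw), and DF_L = t + g.

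For t = 5%, w = 80%: DF_R = 0.05 × 0.20 / (1 − 0.04) = 0.010 / 0.96 = 1.04%. With g = 0, DF_L = 5.00%, and the rule returns 1.04%.

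| t | g | w | DF_R | DF_L | Adjusted | DF_L − DF_R (points) |
|---|---|---|---|---|---|---|
| 5% | 0 | 0 | 5.00% | 5.00% | 5.00% | 0 |
| 5% | 0 | 50% | 2.56% | 5.00% | 2.56% | 2.44 |
| 5% | 0 | 80% | 1.04% | 5.00% | 1.04% | 3.96 |
| 5% | 0 | 100% | 0 | 5.00% | 0 | 5.00 |
| 5% | 3 points | 0 | 5.00% | 8.00% | 5.00% | 3.00 |
| 5% | 3 points | 80% | 1.04% | 8.00% | 1.04% | 6.96 |
| 2% | 0 | 80% | 0.41% | 2.00% | 0.41% | 1.59 |
| 10% | 0 | 80% | 2.17% | 10.00% | 2.17% | 7.83 |

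The adjusted figure minus the retailer figure is zero in every row. The rule is right when nothing is withheld (rows 1 and 5). Once packs are withheld, the whole shortfall carries over.

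**Step 3: what the unadjusted difference can show.** In row 2 a gap of 2.44 points comes entirely from withholding; in row 5 a gap of 3.00 points comes entirely from legal purchases. The raw difference keeps the signal that the rule deletes, but it cannot by itself say which cause is at work.

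**Step 4: sampling error.** The smaller of two noisy proportions averages below the truth when both true values are equal. At 2% in both sources, with an assumed 50 packs per street per source pooled over 80 streets (4,000 packs each) and simple binomial sampling, the mean is 1.88%, a shift of 0.12 points. If litter truly holds more, say 3% against 2%, the standard error of the difference is √(0.03 × 0.97/4,000 + 0.02 × 0.98/4,000) = 0.35 points. The one-point difference is then about 2.9 standard errors and the bias is close to zero.

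**The case against.** The best reply is that litter cannot tell a legally bought duty-free pack from an illegally sold one, so any single figure needs an assumption, and the article declares the one it makes. It also keeps three databases with separate estimates, and both raw proportions must be computed before the rule can be applied. Nothing says outright that the adjusted values are the ones compared. This stands in part: the article does not promise an unadjusted comparison either, and the only street and trash duty-free estimate it defines is the capped one.

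A reader might infer more than the text supports:

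- **That the street and trash sources cannot check retailers at all.** The formula covers duty-free packs, one of seven attributes in section 3. Price marking, brand elements, the two kinds of health warning, the declaration and the tax stamp have no stated cap, and the sources can still differ on them.
- **That agreement is always forced.** Equality is forced only when DF_L > DF_R. When DF_L is smaller, the rule returns DF_L and the difference stays visible.
- **That packs bought in neighbouring countries stay counted as illicit.** Table 3 indicates adjustment for the ambiguous street and trash packs. A formula not printed for each row may sit in the fuller protocol.
- **That taking the minimum roughly halves the estimate.** A mean of 0.96% against 2% arises only if the rule is applied street by street with an assumed 50 packs per source. The article states no such calculation.
- **That the retailer estimate for question (a) is distorted.** Table 3 applies no adjustment to retailer packs.

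**Conclusion.** The point holds for the duty-free component. As written, the adjusted street and trash figure is at most the retailer figure and equals it whenever litter shows more duty-free packs. Retailer withholding or full-pack sale of illegal duty-free packs therefore passes through undiminished, and the stated rule defeats the stated check. This part follows from the algebra and needs no assumption.

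The size depends on shares the article does not give. Under the assumed true shares of 2%, 5% and 10% with 80% withheld and no legal duty-free packs in litter, the adjusted figure falls short by 1.59, 3.96 and 7.83 points. For scale, the only national illicit share cited in the introduction is an industry-derived figure of about 2%. The downward pull from sampling error is minor on pooled data and is not the reason to change the plan. How far the total illicit share or the overall cross-source comparison would move cannot be determined from the article.

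**What to change.** 1. Report unadjusted DF_L, and its trash equivalent, beside DF_R.
2. For street and trash, give the illicit share as a range: packs that are illicit only because they are duty-free are all counted legal for the lower limit and all counted illegal for the upper.
3. Keep min(DF_L, DF_R) only as a labelled sensitivity analysis on pooled proportions, and do not cite it as evidence of agreement.
4. Base the cross-source check, including the validation of the trash method, mainly on attributes that need no adjustment. Show the unadjusted duty-free difference as well, with the caveat that an excess in litter may be legal purchase or retailer withholding. Unadjusted proportions alone should not carry the check, because legal purchases could then look like disagreement.
5. Treat packs bought in neighbouring countries with the same range, so that the text and Table 3 agree. This matters in a design with 60 of 80 post codes in border districts.
6. Amend section 4 so that it no longer claims that the street and trash estimates resolve retailer under-reporting for duty-free packs.

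No new data are needed. The cost is revised wording, one extra table, and street and trash results stated as ranges rather than single figures.
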